#### Secondary objectives

Cardiorespiratory fitness (VO_2_ max), blood pressure and body composition, measured at baseline and after nine months (post-intervention).Self-reported health and health-related quality of life (HRQoL), assessed at baseline, after three months, six months and nine months (post-intervention).Experiences with bicycling and intrinsic motivation for bicycling, explored after three months, six months and nine months (post-intervention).

#### Other study objectives

4.How season and weather conditions influence amount of bicycling.5.Potential spill-over effects on participants’ partners.

## Methods

### Study design

The present study will have a cross-over design, entailing that participants in the intervention group (*n* = 18) will complete the following intervention arms in random order: (i) three months access to an e-bike with trailer (*n* = 6), (ii) three months access to a longtail bike (*n* = 6), and (iii) three months access to a traditional bike with trailer (*n* = 6), in total nine months. Also, a control group (*n* = 18) maintaining usual transportation and PA habits will be included. Randomization of participants into intervention or control group will be stratified according to sex and cardiorespiratory fitness. As incentive for participants randomized into the control group, those who fulfill the study will be in the draw of one traditional bicycle, including a trailer. To reduce the risk of accidents and injuries, bike helmets (parent and child), a reflex vest, lights and winter tyres with spikes will be handed out. The present study was approved by The Norwegian Social Science Data Services (NSD), and all participants will provide informed consent prior to study start. The trial is registered at clinicaltrials.gov, with number NCT03131518.

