### Study sample

A convenience sample consisting of 36 parents of toddlers residing in Kristiansand municipality, Southern Norway, will be recruited. Main outcome will be total amount of bicycling (distance and time). Due to few previous studies in e-bikes and none in longtail bikes targeting total amount of bicycling, power calculations are challenging to perform. However, based on a standard deviation (SD) of 60 min/week [48], a power of 0.80 and a significance level of 5%, we will be able to detect an increase in cycling time from 15 min (based on inclusion criteria) to 75 min a week (i.e. half of weekly PA recommendations) with 16 subjects in the intervention group and 16 subjects in the control group. Yet, to account for 10% drop-out, and to utilize the bikes optimally according to the study design (see Table 1), we will include 18 subjects in both groups (intervention and control). Inclusion criteria are: (i) being able to understand and read Norwegian, (ii) having one child born in year 2013, 2014 or 2015, attending kindergarten, (iii) being responsible for bringing/picking up the child in the kindergarten ≥5 times per week/at least half of the times, (iv) residing 2–10 km from the workplace, (v) residing <3 km from the kindergarten and the grocery shop, (vi) having car-access (vii) possessing a smartphone requiring personal pin code or comparable safety solution for usage, (viii) being between 167 and 190 cm tall (due to the size of accessible bikes), and (ix) have the opportunity to store the bikes indoors. Exclusion criteria are: (i) being physically active, i.e. meeting the PA recommendations [1, 45], (ii) having bicycled more than once weekly during the last twelve months to the workplace, kindergarten or the grocery shop, and (iii) suffering from severe cardiovascular diseases or upper respiratory tract diseases.

**Table 1 Tab1:** Possible combination of intervention arms

Month 1–3	Month 4–6	Month 7–9	
E-bike	Longtail	Traditional	*n* = 3
E-bike	Traditional	Longtail	*n* = 3
Longtail	E-bike	Traditional	*n* = 3
Longtail	Traditional	E-bike	*n* = 3
Traditional bike	E-bike	Longtail	*n* = 3
Traditional bike	Longtail	E-bike	*n* = 3

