### Quantitative and qualitative data analyses

The statistical analyses for the quantitative data will be performed using the statistical software package IBM SPSS Statistics version 24.0 (IBM Corp., Somers, New York, USA). A two-sided *p*-value of <0.05 will be considered statistically significant. Descriptive analyses will be conducted and continuous variables will be presented as means and standard deviations (SD), categorical variables as proportions. Moreover, regression analyses will be performed according to Twisk and Proper [73], using data from the post-measures adjusting for baseline measures, to assess differences between (1) the control group and the intervention group (between design) for all outcome variables, and (2) within the intervention group when comparing the three different arms regarding total amount of bicycling and PA, transportation habits, and self-reported health and HRQoL.

A qualitative content analysis will be conducted from a phenomenologic-hermeneutic perspective [74]. Recordings of the qualitative interviews will be transcribed verbatim and read repeatedly to grasp the meaning of the data as a whole. Data will then be imported into the software analysis program NVivo 11 for further analysis. The next step will be to separate the text into meaning units; i.e. the words, sentences or paragraphs containing aspects related to each other through their content and context. Following this, the meaning units will be classified into subcategories, by pooling data with similar characteristics together in a category defined by its content. Finally, the subcategories will be combined and categorized into main categories.

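### The between-group model does not name the stratification factors, sex and fitness; if they predict cycling, leaving them out makes the main test conservative (minor)

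*Protocol article*

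**What the plan says.** Under Study design, the allocation is described as follows: "Randomization of participants into intervention or control group will be stratified according to sex and cardiorespiratory fitness". The number of fitness levels is not given.

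Under Quantitative and qualitative data analyses, the model is a regression "using data from the post-measures adjusting for baseline measures", used to compare "the control group and the intervention group (between design) for all outcome variables". This is the only description of the quantitative model. It does not define the baseline measures, and it mentions neither sex nor fitness.

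Under Study sample, the main outcome is cycling distance and time. The sample size rests on "an increase in cycling time from 15 min (based on inclusion criteria) to 75 min a week", an SD of 60 min/week, power 0.80 and a 5% level, which gives 16 per group, raised to 18 for 10% drop-out. One exclusion criterion is "having bicycled more than once weekly during the last twelve months to the workplace, kindergarten or the grocery shop".

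**The concern.** Stratified allocation balances the groups on sex and fitness, so chance imbalance in these factors no longer adds to the true variance of the treatment estimate. A model without the factors still counts their contribution as residual noise. The reported standard error is then larger than the true one, the interval is too wide, and the type I error falls below 5%.

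The wording pairs post-measures with baseline measures, which most naturally means each outcome's own baseline value. Sex has no post-measure, and baseline VO2max is not the baseline of cycling time. The outcome's own baseline may not make up for this: frequent transport cyclists are excluded, so baseline cycling is restricted and probably explains little of later cycling.

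At stake is precision on the main outcome in a trial of 36 people, whose Discussion itself lists sample size and power as shortcomings.

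**Working it through.** **Inputs from the article.** Difference 75 − 15 = 60 min/week; SD 60; two-sided 5%; power 0.80; 16 analysed and 18 enrolled per group; 10% drop-out (all Study sample, except two-sidedness, which is in the analysis section). Stratification by sex and fitness (Study design).

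**Assumptions.** R², the share of variance in cycling time that sex and fitness explain beyond baseline, is not given; the range 0 to 0.30 is assumed. Four equal strata with 1:1 allocation within each are also assumed.

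**1. The plan's own figure.** n per group = 2(1.960 + 0.842)² × (60/60)² = 15.7, so 16. With drop-out, 16/0.90 = 17.8, so 18. Both reproduce. Power at 16 per group is 0.807 by the normal approximation and 0.781 by the noncentral t. No covariate enters the calculation.

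**2. Excess in the standard error.** With 32 analysed and balanced strata, the unadjusted model puts the whole stratum sum of squares into a residual with 30 degrees of freedom. The ratio of the unadjusted to the adjusted standard error is about √[1 + (32/30) × R²/(1 − R²)]:
- R² = 0.10: √(1 + 1.067 × 0.111) = 1.058
- R² = 0.20: √(1 + 1.067 × 0.250) = 1.125
- R² = 0.30: √(1 + 1.067 × 0.429) = 1.207

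**3. Power, type I error and interval width.** Simulated trials, 16 + 16, regression with and without the two factors:

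| R² | SE too large by | Type I error without | Power without | Power with | 95% half-width without / with (min/week) |
|---|---|---|---|---|---|
| 0.10 | 6% | 3.9% | 79% | 82% | 43.0 / 40.8 |
| 0.20 | 13% | 2.6% | 80% | 86% | 43.3 / 38.6 |
| 0.30 | 21% | 1.8% | 82% | 91% | 43.5 / 36.1 |

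The gains are 3, 6 and 9 points. As a check, the noncentral t with residual SD 60√(1 − R²) and 28 degrees of freedom gives adjusted power of 0.821, 0.863 and 0.904. Setting these against a fixed 0.781 would give gains of about 4, 8 and 12 points. That overstates the gain, because stratified allocation already raises the unadjusted power slightly.

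**4. If the factors explain nothing.** The noncentral t gives 0.781 without the factors and 0.779 with them. Simulated losses are 0.2 to 0.4 points.

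**5. If controls hardly vary.** Suppose the factors act almost only in the intervention group. The pooled coefficient is then about half the intervention-group coefficient, so it explains (1/2)² = 1/4 of that group's prognostic variance. The total variance, averaged over both groups, is about 1/2 of that group's variance. The effective R² is (1/4)/(1/2) = half. Simulation with the control SD at one tenth of the intervention SD, and 10%, 20% and 30% explained within each group, gives a standard error about 3%, 6% and 10% too large and gains of about 1.5, 3 and 5 points.

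**The case against.** The strongest objection is that the article does not say the strata are left out. The term for baseline measures is undefined, sex and VO2max are both collected at baseline, and a full covariate list often sits in an analysis plan that is not shown. A reader might infer that the model adjusts only for the outcome's own baseline; that is the natural reading, but the word "only" is not in the text. What stands is narrower: the article states a model for the comparison it randomises and does not name the factors it randomises by.

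The second objection is that the size is unknown, and this stands. The Background gives qualitative reasons to expect some effect: it lists poor fitness as a barrier to cycling and describes mothers as under-represented among cyclists. It gives no figure. Eligibility also excludes people who meet the activity recommendations, which probably narrows the fitness range. The upper R² values may therefore be optimistic, and step 5 may be nearer the truth.

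A reader might further infer that the trial loses planned power, is biased, or has an inflated false-positive rate. None of this follows. The 16 per group assumes no covariates, unadjusted power stays at about 79% to 82%, the estimate is unbiased, and the type I error is below 5%. The 0.781 from the noncentral t reflects the normal approximation in the sample size, not the strata.

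Nor can baseline cycling be called zero for everyone. The exclusion covers cycling more than once weekly to three destinations, and the sample size itself assumes 15 min/week.

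**Conclusion.** The point holds as a minor one. The stated between-group model does not name the two stratification factors, and for cycling time and distance the natural reading omits them. The consequence is conditional: the comparison is conservative to the extent that sex and fitness predict cycling beyond baseline.

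The trade favours adjustment: at most a fraction of a point of power lost if the factors are irrelevant, against a gain of a few points, and up to about 9, if they matter. These sizes rest on the assumed R², on four equal balanced strata and on 16 analysed per group. The loss is relative to an adjusted analysis, not to what the protocol promised.

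**What to change.** State in the analysis section that every intervention-versus-control model includes sex and baseline VO2max (continuous) next to the baseline value of the outcome. When VO2max is the outcome, its baseline value already serves, so add only sex; otherwise the same variable would enter twice.

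The cost is one sentence and one or two degrees of freedom. Sex is supplied at sign-up, and fitness has to be known before stratified allocation, so no new data are needed.

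Home-to-work distance may look like a useful further covariate for cycling. It should not be required on this ground: it is not a stratification factor, and the article shows only that the 2–10 km eligibility range is checked, not that the distance is recorded as a value.

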### Study sample

A convenience sample consisting of 36 parents of toddlers residing in Kristiansand municipality, Southern Norway, will be recruited. Main outcome will be total amount of bicycling (distance and time). Due to few previous studies in e-bikes and none in longtail bikes targeting total amount of bicycling, power calculations are challenging to perform. However, based on a standard deviation (SD) of 60 min/week [48], a power of 0.80 and a significance level of 5%, we will be able to detect an increase in cycling time from 15 min (based on inclusion criteria) to 75 min a week (i.e. half of weekly PA recommendations) with 16 subjects in the intervention group and 16 subjects in the control group. Yet, to account for 10% drop-out, and to utilize the bikes optimally according to the study design (see Table 1), we will include 18 subjects in both groups (intervention and control). Inclusion criteria are: (i) being able to understand and read Norwegian, (ii) having one child born in year 2013, 2014 or 2015, attending kindergarten, (iii) being responsible for bringing/picking up the child in the kindergarten ≥5 times per week/at least half of the times, (iv) residing 2–10 km from the workplace, (v) residing <3 km from the kindergarten and the grocery shop, (vi) having car-access (vii) possessing a smartphone requiring personal pin code or comparable safety solution for usage, (viii) being between 167 and 190 cm tall (due to the size of accessible bikes), and (ix) have the opportunity to store the bikes indoors. Exclusion criteria are: (i) being physically active, i.e. meeting the PA recommendations [1, 45], (ii) having bicycled more than once weekly during the last twelve months to the workplace, kindergarten or the grocery shop, and (iii) suffering from severe cardiovascular diseases or upper respiratory tract diseases.

**Table 1 Tab1:** Possible combination of intervention arms

Month 1–3	Month 4–6	Month 7–9	
E-bike	Longtail	Traditional	*n* = 3
E-bike	Traditional	Longtail	*n* = 3
Longtail	E-bike	Traditional	*n* = 3
Longtail	Traditional	E-bike	*n* = 3
Traditional bike	E-bike	Longtail	*n* = 3
Traditional bike	Longtail	E-bike	*n* = 3

### Measurements

#### Questionnaire survey

When signing up and providing consent electronically, parents will supply relevant background information such as gender, age, ethnicity, education, income and occupational status, and information allowing to determine eligibility for inclusion. Moreover, a web-based questionnaire will assess transportation habits, self-perceived health and HRQoL [64], and determinants for bicycling, e.g. intrinsic motivation [52], at baseline and post all intervention arms, i.e. in total four times. Participant’s partners will be requested to fill in the questionnaire at baseline and post-intervention, to assess potential spill-over effects.

#### Bicycle use and total physical activity level

Total amount of bicycling (i.e. cycling distance, time and pace) will be measured with a cycle computer and an appropriate smartphone application, the latter being developed at UiA in cooperation with Department of Information and Communication Technology. The app shall include a diary-function, enabling registration of bicycle type (el/longtail/traditional) and trip purpose. Total time of MVPA will be measured for seven consecutive days at study start and connected to each intervention arm (at 3, 6 and 9 months), using the monitor SenseWear Armband Mini (SWA; BodyMedia, Pittsburgh, Pennsylvania, USA). Data will be downloaded using the software SenseWear Professional V.8.1 (BodyMedia, Pittsburgh, Pennsylvania, USA), with a valid day defined as at least 80% (19.2 h) wearing time. To be included in the analyses, participants need to provide a minimum of four valid days, comprising at least one weekend day [65, 66]. The cut-off defining MVPA will be 3 METs [67]. In addition, seasonal variations in bicycling amount will be explored, and weather data (temperature, rainfall, snow, etc.) will be collected.

#### Physiological parameters

At baseline and post-intervention, cardiorespiratory fitness (VO_2_ max, minute ventilation (VE) and respiratory exchange ratio (RER)) will be measured performing treadmill walking/running to exhaustion, using a modified Balke-protocol according to Edvardsen et al. [68]. Heart rate (HR) will be registered every minute using the heart rate sensor Polar M400 (Polar Electro, Oy, Kempele, Finland). Time to exhaustion will be measured as minutes from start to test completion, i.e. reaching VO_2_ max. Criteria for acceptable VO_2_ max will be determined according to sex and age, as described by Edvardsen et al. [69]. In order to measure body composition (i.e. the distribution of fat mass, non-bone lean mass and bone mineral density) rapid and accurately, dual-energy X-ray absorptiometry (DXA; GE-Lunar Prodigy, Madison, WI, USA) will be used [70, 71]. In addition, blood pressure will be measured with the monitor Microlife BP A100 (Widnau, Switzerland), and body weight and height (height only at baseline) will be measured to the nearest 0.1 kg and 0.5 cm, respectively, with participants wearing light clothes and no shoes. Oral and written instructions will be provided prior testing, and all measurements will be performed by the same test leaders and in the same order each time.

#### Qualitative interviews

Apart from the influence of accessibility on total amount of bicycling [50], and the feasibility of bicycling for transportation, we also want to address intrinsic motivation as one relevant determinant, guided by Self-determination theory (SDT) [52]. Thus, participants in the intervention group (*n* = 18) will be invited to take part in semi-structured qualitative interviews after three months, six months and at study completion. Data collection method will be focus group interviews (*n* = 6 in each group, combining individuals using the same type of bike), to obtain a nuanced investigation of the aspects of interest, based on group discussions and interactions between the participants [72]. To examine the feasibility of using different bicycle types for transportation, main focus for the interviews will be exploration of participants’ experiences with usage of the different bicycle types, and further intrinsic motivation [63] for bicycling. One trained interviewer (with public health background) will lead the interviews, while an assistant will be present for observation.

### Quantitative and qualitative data analyses

The statistical analyses for the quantitative data will be performed using the statistical software package IBM SPSS Statistics version 24.0 (IBM Corp., Somers, New York, USA). A two-sided *p*-value of <0.05 will be considered statistically significant. Descriptive analyses will be conducted and continuous variables will be presented as means and standard deviations (SD), categorical variables as proportions. Moreover, regression analyses will be performed according to Twisk and Proper [73], using data from the post-measures adjusting for baseline measures, to assess differences between (1) the control group and the intervention group (between design) for all outcome variables, and (2) within the intervention group when comparing the three different arms regarding total amount of bicycling and PA, transportation habits, and self-reported health and HRQoL.

A qualitative content analysis will be conducted from a phenomenologic-hermeneutic perspective [74]. Recordings of the qualitative interviews will be transcribed verbatim and read repeatedly to grasp the meaning of the data as a whole. Data will then be imported into the software analysis program NVivo 11 for further analysis. The next step will be to separate the text into meaning units; i.e. the words, sentences or paragraphs containing aspects related to each other through their content and context. Following this, the meaning units will be classified into subcategories, by pooling data with similar characteristics together in a category defined by its content. Finally, the subcategories will be combined and categorized into main categories.

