The strengths of the present study are firstly that the intervention is being conducted in a natural setting with accessibility to different bicycle types representing the intervention arms, and no instructions in terms of bicycling amount. Thus, the effect of accessibility on voluntary cycling (distance, time and pace) and potential health effects can be examined - in other words, both effectiveness and efficacy [78]. As discussed herein, we need increased knowledge regarding potential health effects (efficacy) of using e-bikes and longtail bikes for transportation. Still yet, public health and environmental gains will be attenuated if it turns out that bicycling for transportation does not represent a feasible mode of transport for parents with children attending kindergarten, and “compliance” (bicycling) is low (effectiveness), meaning that both effectiveness and efficacy are relevant aspects. In this regard, inclusion of semi-structured qualitative interviews will enrich the study, as it allows for an exploration of participants’ experiences and pros and cons with bicycling for transportation, when using different bicycle types. An additional advantage is that the cross-over design (within design) removes variability between subjects and thus increases power, compared with a parallel group design (between design). Also, as opposed to a between design, comparability of subjects within conditions is enabled. Further, the use of a reference method for assessing body composition (DXA), and objective measures of total levels of MVPA (SWA) and amount of bicycling (cycle computer and smartphone-app), are study strengths.

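### The three-bike comparison is assigned the same baseline-adjusted regression as the control comparison, with no participant or period term named, so the precision claimed for the cross-over would not reach its standard errors and tests

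*Protocol article*

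**What the plan says.** In the protocol article, the section on quantitative and qualitative data analyses specifies regression "using data from the post-measures adjusting for baseline measures, to assess differences between (1) the control group and the intervention group". The same sentence applies this method to a second comparison, "within the intervention group when comparing the three different arms regarding total amount of bicycling and PA", which also covers transportation habits, self-reported health and quality of life. Baseline is the only adjustment named. The method is referred to a cited methods paper.

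Under Study design and Table 1, every intervention participant uses all three bikes, in one of six orders with three people each. The objectives list one baseline assessment, followed by assessments at three, six and nine months.

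The Discussion counts it as a strength that "the cross-over design (within design) removes variability between subjects and thus increases power, compared with a parallel group design". Its limitations paragraph accepts that period and carry-over effects may influence the comparison across bike types, and that sample size and power are shortcomings.

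**The concern.** A cross-over gains precision because each person serves as their own control. The gain appears in standard errors and p-values only if the model recognises that three records come from one person. The model as described does not do this.

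Baseline adjustment is no substitute. The baseline is a single pre-study value, identical across a participant's three records, so it cancels from any within-person difference between bikes. It removes between-person variance only as far as it predicts later behaviour. For cycling that is doubtful, because people who cycled to work, kindergarten or the shop more than once weekly are excluded, which narrows the range of the covariate.

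No period term is named either, although the Discussion expects period effects to be possible. Table 1 balances bikes over periods, so with complete data an omitted period effect does not bias the bike contrasts. It does stay in the residual variance.

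At stake is the ability to show differences between e-bike, longtail and traditional bike on the main outcome, in a trial with only 18 people in that comparison.

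**Working it through.** **The plan's own figure.** The Study sample section aims to "detect an increase in cycling time from 15 min (based on inclusion criteria) to 75 min a week" "with 16 subjects in the intervention group and 16 subjects in the control group", with SD 60 min/week, power 0.80 and 5% significance. The normal formula gives 2 × (1.96 + 0.8416)² × 60² / 60² = 15.7, so 16 per group (power 0.807). The exact t-test gives 0.781 at 16 and 0.807 at 17, which is close enough. Allowing for 10% drop-out, 16 / 0.9 = 17.8, so 18. The figure reproduces, but it concerns intervention versus control only. The article states no power for the bike contrasts.

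**Inputs for a bike contrast**
- 18 participants × 3 periods = 54 records (Study design, Table 1).
- Total SD 60 min/week (Study sample).
- Two-sided 5% level (analysis section).
- Within-person correlation ρ between bike periods: not given. Assumed 0 to 0.7.
- Correlation r of baseline with later cycling: not given. Taken as 0, then varied to 0.5.

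**Formulas**
- Reported standard error, baseline-only regression: 60 × √(2(1 − r²)/18). With r = 0 this is 60 × √(2/18) = 20.0.
- True standard error of the contrast, which a participant effect recovers: 60 × √(2(1 − ρ)/18) = 20.0 × √(1 − ρ).
- Actual type I error of the baseline-only test (normal approximation): 2 × [1 − Φ(1.96 × ratio)], where ratio is reported over true standard error.
- Difference detectable with 80% power: 1.96 × reported SE + 0.8416 × true SE.

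| ρ (assumed) | SE as written | SE with participant effect | Ratio | Type I error as written | Detectable as written | Detectable with participant effect |
|---|---|---|---|---|---|---|
| 0 | 20.0 | 20.0 | 1.00 | 5.0% | 56 | 56 |
| 0.3 | 20.0 | 16.7 | 1.20 | 1.9% | 53 | 47 |
| 0.5 | 20.0 | 14.1 | 1.41 | 0.6% | 51 | 40 |
| 0.7 | 20.0 | 11.0 | 1.83 | 0.03% | 48 | 31 |

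Standard errors and detectable differences are in min/week.

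**An informative baseline.** With r = 0.3 the reported SE is 19.1 and the ratio at ρ = 0.5 falls from 1.41 to 1.35. With r = 0.5 the reported SE is 17.3 and the ratio at ρ = 0.5 is 1.22. The excess shrinks but remains.

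**Simulation check.** The six-sequence design of Table 1 was simulated 3,000 times per scenario with r = 0, comparing regression on bike and baseline with regression on bike, period and participant.
- Point estimates agreed to rounding error in every complete, balanced trial.
- Type I error of the baseline-only analysis was 3.2%, 0.8% and 0.2% at ρ = 0.2, 0.5 and 0.7.
- Power for a 40 min/week bike difference was 49%, 52% and 51% without the participant term and 57%, 80% and 94% with it. The 40 min/week is illustrative and not a figure from the article.

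**The case against.** The strongest reply is that the missing participant effect is inferred from what the sentence does not name. The article speaks of regression analyses without giving their type. Mixed models and models with participant indicators are regressions too, and the cited methods paper is not shown. The second comparison is described as within the intervention group, and the Discussion calls the cross-over a within design, so a repeated-measures analysis may be intended. A journal article also condenses, and model detail may sit elsewhere. This stands to the extent that the article names no participant effect but does not exclude one. It does not dispose of the point, because the article prescribes a method, gives the same one to a parallel and a cross-over comparison, and names baseline as the only adjustment.

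Two stronger readings are tempting and not supported:
- **That the bike estimates lose precision or false positives rise.** With complete, balanced data the estimates are identical under both models, and the error in the reported standard errors is conservative.
- **That the control comparison has a standard error that is too small.** This would follow if three post-measures per person were pooled as independent. The article does not say so. A regression on the nine-month value, or one per time point, fits the text equally well.

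It is also fair that the size depends on a correlation the article does not give, that the restricted baseline range concerns cycling and not the other outcomes, and that power is already listed as a limitation.

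**Conclusion.** The point holds in limited form. The method as described does not match the cross-over part of the design, and following it would not deliver the power gain that the Discussion claims. Reported standard errors for bike differences in cycling time would be too wide by a factor of 1.20 to 1.83 for within-person correlations of 0.3 to 0.7, given SD 60 min/week, 18 complete participants and an uninformative baseline. The factor is 1 at zero correlation and smaller where baseline predicts the outcome. Some positive correlation is plausible, since the same person keeps the same household and commute.

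The consequence is missed differences between bikes. The powered comparison, intervention versus control, is not shown to be affected. Because no power is stated for the bike contrasts and the error is conservative, this is worth correcting before analysis but is not a critical defect.

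**What to change.** For the outcomes assessed at 3, 6 and 9 months (bicycling, physical activity, transportation habits, self-reported health and quality of life), state that the three-bike comparison uses a linear mixed model, or an equivalent suited to the outcome type, with a participant effect and fixed effects for bike type and period. A participant who misses one assessment then still contributes the others.

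Keep baseline-adjusted regression for outcomes with a single post-measure: VO2 max, blood pressure and body composition.

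For the control comparison, state which post-measure or post-measures enter. If more than one per person is used, that model needs a participant effect too.

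The cost is a few sentences in the analysis section. SPSS, the software already named, has a mixed-model procedure, and no further data are needed.
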